## Abstract

**Background:**

Anxiety and depressive disorders in children and adolescents are highly prevalent and account for more than half of all youth psychiatric disorders. Left untreated, anxiety, and depression lead to numerous detrimental outcomes, including reduced quality of life, psychiatric, and somatic comorbidity and even reduced lifespan. This puts a large strain on child and adolescent mental healthcare services (CAMHS) to provide effective treatments. However, even when provided the best evidence-based treatment, between 40–50% of patients continue to report significant symptom burdens. Thus, there is an immediate need for supplemental and/or new treatment approaches. Physical activity as a supplementary treatment may be such an approach. However, research investigating this approach within this population is scant. This protocol paper describes the development and feasibility trial of a physical activity-based intervention targeting anxiety and depressive symptoms in youth treated in CAMHS.

**Methods/design:**

The study is based on the UK Medical Council Research Framework (MRC) for developing and evaluating complex interventions. Feasibility and acceptability of the physical activity intervention (confident, active, and happy youth) will be evaluated in an uncontrolled open-label trial using qualitative and quantitative data. Twenty youths with anxiety and/or depressive symptoms will be recruited. Acceptability of assessment procedures, the intervention, and perceived benefits and barriers to participation will be assessed, and qualitative interviews with participants, caregivers, and referring specialists will explore contextual and practical factors associated with intervention delivery. Physical activity will be measured using the Actigraph GT3X+ monitor at baseline, and post-intervention and change in anxiety and depression will be assessed.

**Discussion:**

This study will contribute to the development of supplementary physical treatment interventions for youth with anxiety and depression in contact with CAMHS. The goal is to examine new avenues of treatment that ultimately may improve upon current treatment outcomes of anxiety and depression. This work will be in preparation for a future definitive randomized controlled trial (RCT) of this approach, in line with the MRC Framework.

**Trial registration:**

ClnicalTrials.gov, NCT05049759. Registered on August 19, 2021. Retrospectively registered.

**Supplementary Information:**

The online version contains supplementary material available at 10.1186/s40814-022-01010-6.

## Background

Internalizing disorders in the form of anxiety and depression are the most common mental health disorders among children and adolescents (hereafter youth), with a prevalence of 6.5% for anxiety disorders (CI 95% 4.7–9.1) and 2.6% for depressive disorders (CI 95% 1.7–3.9) [1, 2]. These disorders tend to develop early in life, and short- and long-term consequences include reduced quality of life, psychiatric and somatic comorbidity, disability, loss of education and/or work, suicide, and reduced life-span [3, 4]. According to the World Health Organization, anxiety, and depressive disorders are major health problems with large-scale societal and economic consequences (WHO, 2017). Anxiety and depression are among the top five causes of overall disease burden among youth in Europe [5].

Discouragingly, even when provided the best evidence based treatment, post-treatment remission rates for anxiety and depressive disorders in youth are just slightly above chance, e.g., 50% (mixed anxiety: 50.7% CI 45.3–56.2; depression: 53.2%, CI 34.6–70.9 [6]. Such suboptimal treatments have adverse consequences for the individual, but also place a large strain on treatment services, which are dependent upon sufficient capacity and effective treatment. If patients do not recover or experience relapse following treatment, these patients require further treatment, thus excluding new patients from gaining access to treatment. In light of the high prevalence of these disorders, short- and long-term consequences, and the suboptimal effect of current treatments, there is a pressing need for development of new and supplementary interventions to improve recovery rates [6–8].

In recent years, physical activity has gained traction as a promising area in effective mental health treatments [9, 10], and physical activity is identified as a key modifiable factor in people with mental illness [11]. Meta-analyses of the effects of physical activity in the treatment of anxiety and depression in adult populations indicate small to moderate effects [12–14]. This knowledge is now implemented in adult depression treatment recommendations such as those provided by The European Psychiatric Association [15]. The amount of research on the topic in paediatrics is substantially less [9, 16]; however, new evidence is starting to accumulate. Three recent meta-analyses investigating the effect of physical activity on youth depression found small to moderate effects [16–18]. Studies examining the effects of physical activity on anxiety disorders in youth are even fewer, with only one meta-analysis. In this meta-analysis, Carter et al. (2021) concluded that physical activity is potentially effective in reducing anxiety symptoms within non-clinical populations of youth, while evidence within clinical (treatment seeking) populations is insufficient to draw any clear conclusions. All these recent meta-analyses call for well-designed research with youth populations—particularly clinical youth populations [16–19].

The mechanisms by which physical activity interventions impact anxiety and depression are complex and multifaceted [20]. Limitations of previous research and/or mixed results have hampered attempts to tease out the specific intervention mechanisms required to cause change. However, the key recent meta-analyses do point to a few common ingredients across the intervention studies which had positive effects. These ingredients included supervised, aerobic-, and group-based activity of moderate-to-vigorous intensity, with participants engaging in activities multiple times per week over a time period of at least 6 to 8 weeks [16–19]. Questions concerning optimum dosage, type of activity, and energy expenditure are still unclear.

Focusing on the more specific mechanisms of effect of physical activity on anxiety and depression in youth, several biological, psychosocial, and behavioral factors are likely to be involved. Neurobiological mechanisms may include processes that are disrupted or dysregulated and potentially modulated by physical activity. Processes may include inflammatory and oxidative stress responses, neurogenesis, modulation of monoamines (e.g., serotonin), and HPA axis regulation [21, 22]. Hillman et al. found that a program targeting cardiorespiratory fitness resulted in increased neural underpinnings of attentional resources on tasks requiring improved inhibition and cognitive flexibility [23]. Deficits in inhibition and cognitive control are associated strongly with anxiety and depression in youth [24].

In regards to psychosocial processes, physical activity can increase opportunities for social interaction, social connectedness, and experiences of mastery and can lead to increased self-efficacy and independence [20, 25]. Problems and deficits within these areas are closely associated with anxiety and depression in youth [26, 27]. Exposure therapy is the treatment of choice for anxiety disorders in youth [6]. Similarly, physical activity is also assumed to affect anxiety and depression through exposure towards an avoided object and/or situation, i.e., physical activity itself induces bodily sensations and reactions that otherwise might be interpreted as symptoms of anxiety and/or be negatively appraised. Exposure to such sensations and reactions in this setting is thus assumed to be associated with non-threatening experiences, leading to normalization of such experiences and a more appropriate interpretation of these (Kandola et al. 2018).

In terms of behavioral mechanisms, physical activity may improve sleep, self-regulation, and coping skills [20]. The interplay of the mechanisms described above is most likely also highly idiosyncratic to the individual, based on their prior beliefs and experiences of physical activity.

### Development of a supplementary intervention

The development of a supplementary physical activity intervention took place in the Child and Adolescent Mental Health Services, Haukeland University Hospital, Bergen, Norway, from 2018 to 2020. A work and management group consisting of clinicians and researchers, and a trial steering committee consisting of stakeholders, clinicians, users, and parents identified key intervention components and a suitable delivery format. In addition, the group identified and outlined necessary organizational infrastructure, internal work procedures, and team composition in order to deliver the treatments effectively.

The target goals of the program link closely to interrelated core symptoms of anxiety and depression: reduced or low levels of physical activity [28], lack of confidence in one’s ability to cope with situations that incites distress and/or fear, and decreased willingness to engage in and avoidance of situations that may incite distress and/or fear [27, 29]. Finally, a core symptom particularly with depression is lowered mood. Taken together, the primary aim of the intervention is to alleviate these core symptoms and supplement ongoing treatment in CAMHS, which translates to helping youth become more *confident, active, and happy,* hence the name of the intervention*:* Confident, Active and Happy Youth (CAH-Y).

The primary aims of the intervention are as follows:Help youth become more confident, more happy and more physically active.Reduce symptoms of anxiety and depression.

Secondary aims of the CAH-Y intervention are as follows:To motivate and support youths with anxiety/depression symptoms to initiate and maintain an active lifestyle and reduce sedentary behavior.To help foster integration of physical activity into current treatment approaches for internalizing disorders in youth in treatment in CAMHS.

While the effects of the physical activity itself are important and required in the intervention, there is also a need to address underlying reasons why youth with anxiety and depression avoid and/or have difficulty doing physical activity. To this end, the CAH-Y intervention draws on Self Determination Theory [25] and Inhibitory Learning Theory [30]. Self Determination Theory provides a framework with which to understand participant experiences with physical activity and their *motivation* (as opposed to avoidance) towards physical activity. The framework focuses on ways to enhance learning and intrinsic motivation concerning both increased activity and behavior and symptom change [25]. More specifically, the intervention attempts to satisfy youths’ basic psychological needs for autonomy (e.g., providing youth with choice), competence (e.g., adapting exercises to meet the needs/fitness levels of students), and relatedness (e.g., promoting an inclusive group environment). Inhibitory learning theory provides a generic framework to understand the bi-directional interaction between cognition, affects, and behavior in regards to anxiety and depression; in particular the role of physical activity avoidance as a coping and affect-regulation strategy that both causes and maintains these disorders [30].

Drawing together these theories and known components, a treatment manual was developed detailing a supervised, therapist-led, group-based physical activity programme involving aerobic exercise bi-weekly over a course of 7 weeks. Further details on the intervention are detailed below in the *intervention* section. The full treatment manual (in Norwegian) is available on request by contacting the corresponding author.

In line with guidance from the UK Medical Council Research Framework (MRC) [31], the present study is an initial step in determining if the developed intervention is feasible and acceptable for youth with internalizing disorders in CAMHS. A mixed-methods approach was chosen to explore indications of participants’ response and view to the intervention and thereby gain a more full understanding of the intervention acceptability [32]. The present study also includes a calculation of effect size estimates for outcome measures to estimate the sample size of a future “definitive” randomized controlled trial (RCT) as defined by the UK MRC.

The principal aims of this study are as follows:To quantify recruitment rate, willingness to participate, attendance, treatment retention, and adherenceTo assess the appropriateness and practicality of the designed intervention in the proposed settingsTo determine the acceptability of recruitment strategies and the intervention by participants and willingness to participateTo assess the appropriateness and acceptability of the assessment toolsTo provide preliminary evidence of effects of the intervention on physical activity, mood, and anxiousness. This evidence will provide an initial indication of whether the intervention can contribute to change within this group. Estimated effect sizes will provide the parameters for a definitive randomized controlled trial.

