## Methods and design

This protocol conforms to guidelines presented in the Consolidated Standards of Reporting Trials (CONSORT) [33] 2010 statement extension for randomized feasibility studies and clinical trial protocols (see Additional file: Table S1). The intervention component is an uncontrolled open-label feasibility trial (hereafter referred to as “the intervention”), utilizing a pre-test–post-test within-subject design. The overall study design is illustrated in Fig. 1 (below), whereas the stages of the enrollment, interventions, and assessments Table 1 below (The SPIRIT table).

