### Comparison group

Participants will serve as their own controls. Pre- and post-treatment results will be compared to inform a future power calculation.

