The semi-structured qualitative interview will apart from feasibility outcomes also assess participant perceptions on PA in general, participant views on the association between PA and mental health, perceptions on the intervention components and the intervention as a whole, views on potential barriers to physical activity, motivation for activity, and participation in school-based physical activity. These questions will be posed at post-treatment and long-term follow-up. Caregivers will be posed the same questions; however, caregivers of youth aged 12 years or above will only receive these questions if the youth has consented to this. Answers to the questions are written down during the interviews and will be analyzed by thematic analysis [44]. An interview with the referring specialist, following the post-treatment interview with the participant, will similarly explore his/her experiences of the intervention including acceptability of procedures, perceived benefits, and difficulties.

An effect-size will be calculated for youth and caregiver reported depression and anxiety symptoms and activity level. Means (*M*) and standard deviations (*SD*) will be used to investigate the effect sizes for change between pre- to post-treatment. These results will help inform the power calculation of the likely required sample size for a future large-scale RCT.

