## Discussion

The aim of the current study is to develop and feasibility test a supplemental physical activity program for youth with internalizing disorders in regular treatment in child and adolescent mental health clinics (CAMHS). In light of high prevalence of anxiety and depression among children and adolescents, negative short- and long-term consequences, poor recovery rates even when provided best available treatment, there is an urgent need for new and/or supplemental treatment approaches. Physical activity may be one such approach. While the effects of physical activity on internalizing disorders in adults are to some degree empirically underpinned, the benefits, and supplemental treatment effects PA may have for youth are only just beginning to evolve. Thus, there exists a clear evidence gap in regards to the effects of PA on youth internalizing disorders and the integration of such an approach in CAMHS. A necessary first step in developing this field and addressing this knowledge gap is developing and feasibility testing a theoretically based physical activity-based intervention targeting anxiety and depressive symptoms in youth. This may be an important step towards addressing the burden and consequences these mental health disorders cause youth and to help provide more effective treatment.

We anticipate that participation in the intervention will result in increases in physical activity from pre- to post-treatment. Similarly, we also expect some improvements in anxiety and depressive symptomatology from pre- to post-treatment. These anticipated changes are hypothesized to map onto positive changes in youth confidence, mood, and physical activity. Concerning feasibility testing, we expect that feasibility estimates for recruitment, completion, and retention will be met, and results of outcome measures will enable an effect-size estimation for future RCT planning. It is anticipated that youth, parents, and referring specialists will find the intervention acceptable. The qualitative component will provide a unique opportunity to gain a rich perspective of the youths and parents experience and acceptability, which is essential towards future evaluation of the CAH-Y intervention.

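### The definitive RCT is to be sized on an uncontrolled pre-post effect, which is not the added effect of CAH-Y over ongoing CAMHS treatment and probably overstates it

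*Protocol article*

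**What the plan says.** Under Development of a supplementary intervention, the article says that the study includes a "calculation of effect size estimates for outcome measures to estimate the sample size of a future" definitive RCT. The last principal aim in the same section adds: "Estimated effect sizes will provide the parameters for a definitive randomized controlled trial".

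Three other sections define the quantity. Methods and design describes an "uncontrolled open-label feasibility trial" with a within-subject pre-test–post-test comparison. Comparison group makes participants their own controls and states: "Pre- and post-treatment results will be compared to inform a future power calculation". Participant-centered outcome measures says that means and standard deviations "will be used to investigate the effect sizes for change between pre- to post-treatment", and continues more cautiously: "These results will help inform the power calculation of the likely required sample size for a future large-scale RCT".

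On concurrent care, the intervention's primary aim includes to "supplement ongoing treatment in CAMHS". Study population and eligibility has youth referred by their attending CAMHS therapist, and the Discussion also places participants in regular CAMHS treatment. The inclusion criteria require anxiety and/or depressive symptoms and reduced daily physical activity.

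**The concern.** An RCT of a supplementary treatment compares usual care plus CAH-Y with usual care alone. Its sample size depends on the difference in outcome between those arms. A pre-post change in one arm estimates something else: the sum of the effect of CAH-Y, the effect of concurrent CAMHS care, natural course, and regression to the mean after selection on symptoms and inactivity. A single-arm study cannot separate these parts, and a larger sample would not help.

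If the parts other than CAH-Y go in the direction of improvement, which is the usual expectation in treated and symptomatic youth, the pre-post effect is larger than the added effect and the RCT is planned too small. At stake is a definitive trial in a vulnerable population that may be unable to answer its own question.

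**Working it through.** **No figure to reproduce.** The article gives no RCT sample size, alpha, power, effect size or SD. Its own target of 20 youth rests on a citation and not on a formula. The numbers below are therefore illustrations under stated assumptions.

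**Step 1: what each design estimates.** Let D be the standardised pre-post change, and f the share of it that would also occur without CAH-Y. The added effect is then δ = (1 − f) × D. The plan observes D; the RCT needs δ. They coincide only if f = 0. The Background section cites remission of 50.7% (mixed anxiety) and 53.2% (depression) after best evidence-based treatment. This makes f = 0 unlikely, but it does not measure f over seven weeks in this population.

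**Step 2: RCT size if D is used.** Assumptions: two arms 1:1, two-sided 5%, 80% power, D = 0.5 with SD 1. The normal approximation is n per arm = 2 × (1.960 + 0.842)² / d² = 15.70 / 0.25 = 62.8, so 63. The noncentral t calculation gives 64, which is used below.

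**Step 3: power at 64 per arm if the added effect is smaller.** The noncentrality is δ × √(64/2), with 126 degrees of freedom.

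| True added effect δ | Implied f = 1 − δ/0.5 | Power at 64 per arm | Needed per arm for 80% |
|---|---|---|---|
| 0.5 | 0% | 80% | 64 |
| 0.4 | 20% | 61% | 100 |
| 0.3 | 40% | 39% | 176 |
| 0.2 | 60% | 20% | 394 |

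Required size grows as 1/(1 − f)²: 1.78-fold for f = 25%, 4-fold for 50%, 16-fold for 75%. Power for the added effect in a trial sized on D is then about 56%, 29% and 10%, almost regardless of D (checked for D from 0.4 to 0.8).

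**Step 4: precision, apart from bias.** With SE(d) = √[2(1 − r)/n + d²/(2n)], d = 0.5, n = 20 and pre-post correlation r = 0.5 (assumed), SE = √(0.0500 + 0.00625) = 0.237. The 95% CI is 0.5 ± 1.96 × 0.237, or 0.04 to 0.96. With r = 0.3 it is −0.04 to 1.04; with r = 0.7 it is 0.13 to 0.87. So even an unbiased estimate of this size would be too imprecise to fix an RCT sample size.

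**Step 5: do the caveats cover this?** Progression criteria and Statistics and data analysis concede only a lack of statistical power. Limitations of the research mentions the missing control group in connection with blinding. No section says that the pre-post change includes the effect of ongoing treatment, natural course or regression to the mean.

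**The case against.** The strongest reply is that nothing in this study depends on the effect size. The progression criteria are serious adverse events, recruitment and retention. A later trial would need its own sample-size justification, and Limitations of the research places a pilot RCT before the definitive one, which could supply a between-arm estimate. The article also calls the evidence preliminary and an initial indication. This stands as a limit on severity. It does not remove the point: the article does not say that the pilot RCT would replace these effect sizes, and its principal aims assign the role to them.

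It can also be said that Comparison group and Participant-centered outcome measures only speak of informing, or helping to inform, a power calculation. That is compatible with taking SDs from this study. This is fair: the strong wording is confined to Development of a supplementary intervention, and the other two sections need clarification only.

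Some stronger readings are tempting but not supported:
- **The RCT is bound to be underpowered.** This is conditional. Overstatement is the expected direction, but its size is unknown. The Background describes meta-analytic effects of physical activity on youth depression as small to moderate without figures; if the added effect equalled 0.5, 64 per arm would suffice.
- **The plan cannot yield the SD of change.** The article does not name the SD and does not exclude this one; the choice may be left to the full analysis plan. Nor does every RCT calculation need the pre-post correlation: the two-sample sizes above use none.
- **The plan contradicts itself by being underpowered yet estimating effects.** Low power to test a hypothesis does not bar estimation. The fault is in the use made of the estimate.
- **Only 12 of 20 would be analysed because retention may be 60%.** The retention limit is not stated to equal outcome completeness.

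Finally, ongoing CAMHS treatment is not a listed inclusion criterion. It follows from the aim, the referral route and the Discussion.

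**Conclusion.** The point holds in this form: the article makes an uncontrolled pre-post effect size the basis for sizing the definitive RCT, and that quantity is not the added effect of CAH-Y that the RCT would estimate. It probably overstates that effect, because concurrent care, natural course and regression to the mean are likely to act in the same direction.

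The size of the bias cannot be derived from the document. The drop in power from 80% to 61%, 39% or 20% assumes a pre-post d of 0.5, a two-sided 5% test, 1:1 allocation and added effects of 0.4, 0.3 or 0.2. The interval of 0.04 to 0.96 assumes n = 20 and r = 0.5.

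A reader might infer that the feasibility study itself is invalid. It is not: its conduct and its decision on progression do not use the effect size. The point should be fixed, since RCT planning parameters are a declared product of a principal aim, but it is not critical to this study.

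**What to change.** 1. In Development of a supplementary intervention, remove both statements that the effect sizes give the RCT's parameters or sample size.
2. Reword Comparison group and Participant-centered outcome measures so that this study informs the power calculation only through nuisance parameters: the outcome SD, the SD of change and pre-post correlation if a baseline-adjusted analysis is planned, attrition and recruitment, each with a 95% CI.
3. State that the RCT's target difference will come from a minimum important between-group difference, from controlled evidence, or from the pilot RCT mentioned in Limitations of the research.
4. Report the pre-post change descriptively with a 95% CI, and say that it includes ongoing treatment, natural course and regression to the mean.

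The cost is rewording in three sections and a few summary statistics from data already being collected. The downside is that the planned RCT may look larger.
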